#### Co-variates

Sociodemographic characteristics, including the child’s age, gender, parental education level, household income, family structure and ethnicity, will be collected using a questionnaire. The questionnaire also includes questions on other oral health behaviours, such as dietary factors, selected from the questionnaire from Pine et al. [32] (Additional file 2). These variables are collected because they are known moderators of the tooth brushing-related and clinical outcomes, and they therefore need to be adjusted for in the analyses. In addition, information will be extracted from dental records on the restorative and preventive treatments children received during the study, to allow to adjust for this in the analysis and interpretation of data.

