### The intervention

All children, in both the intervention and control group, will receive care as usual, consisting of regular dental check-ups, dental health education following the Ivory Cross national guideline, and if indicated, preventive treatment (fluoride varnish and/or fissure sealants) and/or caries treatment (fillings, non-restorative caries treatment or extractions) [27]. Regular dental check-ups for young children are generally scheduled every 6 months, or at shorter intervals when children are identified as having an increased caries risk. Key oral health messages of the Ivory Cross national guideline include twice daily tooth brushing with fluoride toothpaste (500–750 ppm fluoride), reducing the frequency of carbohydrate intakes to three main meals and a maximum of four (healthy) snacks per day, and avoiding foods and drinks before or during bed time [4]. In addition to care as usual, parents of children in the intervention group will receive supplementary support to adhere to the advice of twice daily tooth brushing with fluoride toothpaste, following the ‘Uitblinkers’ intervention.

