#### Contact moments

The study consists of five contact moments for parents in the intervention group:
T0.0: baseline - visit to the dental practice:Baseline data collection; first interview, including identification of a barrier, discussion of a possible strategy and agreement on an action point.T0.1: 1 month after T0.0 - visit to the dental practice (parent only):Second interview, including follow-up on the progress with the first action point, identification of a second barrier (if present), discussion of a possible strategy and agreement on a second action point.T0.2: 1 month after T0.2 – telephone recall:Telephone recall to follow-up on the progress with the first and second action points.T1: 6 months after T0.0 – visit to the dental practice:Follow-up data collection.T2: 24 months after T0.0 – visit to the dental practice:Follow-up data collection.

Where possible, the research visits at the dental practice will be combined with a regular dental check-up. Parents in the control group will visit the dental practice only at T0.0, T1 and T2 for baseline and follow-up data collection. The interval between T0.0 and T1 is allowed to deviate by 2 months, and the interval between T1 and T2 may vary with 3 months. If parents miss their appointment at T1 and T2, or at T2 only, they will be treated as dropouts. If they only miss the appointment at T1, missing data for T1 will be imputed. Missed telephone recalls will be documented to account for this in the analysis.

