#### Clinical outcome: children’s dental caries experience

At T2, a clinical oral examination will be performed to assess children’s dental caries experience. The clinical oral examination will only include a visual inspection and no x-rays will be taken. Dental caries status will be assessed using the merged International Caries Detection and Assessment System (ICDAS) coding system [35], which classifies dental caries into sound (‘0’), initial stage of decay (‘A’), moderate decay (‘B’) or extensive decay (‘C’). In addition, the dmfs-index will be scored according to WHO Basic Methods for Oral Health Surveys [36]. The oral examinations will be performed by one dentist from each control or intervention practice, after they have received training from a certified ICDAS trainer for calibration and standardisation purposes. The training will be organised 23 months after inclusion of the first participants. During the training, the dentists’ intra- and inter-examiner reliability will be assessed; a minimum weighted kappa of 0.60 for both the intra and inter-examiner reliability is required to certify as an examiner [37]. In case of lower reliability scores, more training will be provided. The dmft and dmfs at baseline will be extracted from personal dental health records from the dental practice, in order to compare differences in dental caries experience between intervention and control children at baseline, and to adjust for potential differences in the analysis.

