### Statistical analysis

All data will be coded with a unique ID, and data will be securely stored at the Department of Social Dentistry at ACTA. The analysis will be performed in STATA. Differences in the primary outcome (dmfs and the combined ICDAS scores ‘B and C’ and ‘A, B and C’) between children in the intervention and control group at T2 will be analysed using zero-inflated Poisson or negative binomial regression. Baseline differences in children’s dmft scores (obtained from dental records) will be taken into account.

Differences in the three tooth brushing-related outcomes between children in the intervention and control group at T1 and T2 will be analysed using ordered logistic or logistic regression (for tooth brushing frequency in children; either treated as a ordinal variable or dichotomous variable, depending on the distribution of responses), and linear or negative binomial regression (for parental self-efficacy scores and children’s plaque scores).

All analysis will be adjusted for clustering of observations within dental practices. In case of significant differences in co-variates (moderators) between the intervention and control group at baseline (T0), the analysis will be adjusted accordingly for these co-variates, or in case of sufficient power, a sub-group analysis will be performed. An intention-to-treat analysis will be conducted to account for participants that will be lost to follow-up. Statistical significance is set at α = 5%.

Qualitative data from the focus group interviews and telephone interviews will be processed using the Maximised Qualitative Data Analysis programme (Verbi-software MAXQDA). Conventional content analysis will be used to identify emergent themes and concepts related to the feasibility and acceptability of the intervention.

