## Abbreviations

ASA: American Society of Anaesthesiologists
dmfs: Decayed, missing and filled surfaces
dmft: Decayed, missing and filled teeth
ICDAS: International Caries Detection and Assessment System
OHP: Oral healthcare professional
WHO: World Health Organization

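### Adjusting the dmfs comparison for restorative treatment received during the study conditions on part of the outcome and biases the effect toward zero, by an amount the protocol does not determine

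*Protocol article*

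**What the plan says.** Five places in the protocol article bear on this point.

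- **Co-variates.** Besides sociodemographic and behavioural variables, records are searched for "restorative and preventive treatments children received during the study, to allow to adjust for this in the analysis" and in interpreting the data. Adjustment is thus a stated purpose of collecting the data.
- **Outcome.** At T2, "the dmfs-index will be scored according to WHO Basic Methods for Oral Health Surveys", and the abbreviation list gives "dmfs: Decayed, missing and filled surfaces". The Statistical analysis section opens its model description with "Differences in the primary outcome (dmfs and the combined ICDAS scores ‘B and C’ and ‘A, B and C’) between children".
- **The intervention.** Usual care in both groups covers "caries treatment (fillings, non-restorative caries treatment or extractions" and, "if indicated, preventive treatment (fluoride varnish and/or fissure sealants".
- **Statistical analysis.** The adjustments named are baseline dmft, clustering within practices, and covariates that differ significantly at T0. Treatment received during follow-up is neither listed nor ruled out. An intention-to-treat analysis is specified.
- **Contact moments.** "Missed telephone recalls will be documented to account for this in the analysis". The telephone recall (T0.2) belongs to the intervention group's schedule; control parents are seen only at T0.0, T1 and T2.

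**The concern.** Fillings and extractions done for caries between T0.0 and T2 make up the f and m of dmfs. They also lie downstream of the intervention: if better brushing prevents cavities, it prevents fillings. A model that holds restorative treatment equal between the groups compares children with the same amount of treated disease, so part of the prevented disease drops out of the contrast. Such a variable cannot do the work of a baseline confounder, and the bias runs toward no effect.

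This matters because the Outcome measures section sets a firm threshold. The intervention counts as successful only with a 25% reduction in caries experience, and favourable brushing outcomes cannot make up for a miss. A fairly small loss can therefore change the declared result.

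Preventive treatment raises a different issue. Varnish and sealants are not counted in dmfs. They are given on indication after baseline, so they may respond to a caries risk that the intervention alters, and they may also reflect how practices differ.

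**Working it through.** **The plan's own threshold.** The control mean for planning is 6.9 dmfs with SD 6.2, and the target difference is 2.0 (Power calculation).

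- 25% of 6.9 = 0.25 × 6.9 = 1.725 dmfs. This lies within the 1.5 to 2.0 dmfs that the Outcome measures section equates with 25%.
- Planned effect: 2.0 / 6.9 = 29%; rate ratio 4.9 / 6.9 = 0.71.
- Share of the planned effect needed to meet the rule: 1.725 / 2.0 = 86%. The tolerable loss is therefore about 14%. On the ratio scale the rule is a rate ratio of 0.75 or lower.

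**Assumptions for the size of the bias.** The article does not give the share of carious surfaces treated during follow-up, so 10% to 90% was assumed. It gives no coding either, so a count of treated surfaces and an any-treatment yes/no indicator were both tried.

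**Simulation.** dmfs was negative binomial, with mean 6.9 and SD 6.2 in controls (shape k = 6.9² / (6.2² − 6.9) = 1.51) and mean 4.9 with the same k in the intervention group. There were 100,000 children per group, no clustering, and all caries was taken as arising during follow-up. Each carious surface was treated with probability p, where p was either the same for every child or varied strongly between children (beta distribution, concentration 1). dmfs was regressed on group, without and with the treatment covariate. Without it the difference was about −2.0. With it, the percentage of the difference that remained was:

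| Share treated | Count, same p | Count, varying p | Yes/no, same p | Yes/no, varying p |
|---|---|---|---|---|
| 10% | 64 | 91 | 76 | 97 |
| 25% | 37 | 79 | 74 | 94 |
| 50% | 17 | 55 | 79 | 90 |
| 75% | 6 | 28 | 86 | 88 |
| 90% | 2 | 12 | 86 | 88 |

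Negative binomial regression, one of the planned models, shows the same pattern. On the log rate ratio, 5% to 94% remains with a count and 70% to 98% with yes/no. The adjusted rate ratios can be set against 0.75:

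- Count, same p: 0.795 to 0.984, so all five shares miss.
- Count, varying p: 0.722 and 0.743 at 10% and 25% treated (met); 0.792, 0.870 and 0.934 at 50%, 75% and 90% (missed).
- Yes/no, same p: 0.774, 0.787, 0.776 and 0.753 at 10% to 75% (missed); 0.744 at 90% (met).
- Yes/no, varying p: 0.713 to 0.739, so all are met.

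**Second set of assumptions.** Here baseline dmfs had mean 1.5; new surfaces had mean 5.4 in controls and 32% fewer in the intervention group; there were 160 children per group and 300 replicates; a linear model adjusted for baseline.

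- Count: −1.70 becomes −0.53 at 30% treated (31% left), −1.76 becomes −0.30 at 50% (17%), and −1.73 becomes −0.14 at 70% (8%).
- Yes/no: −1.23, −1.33 and −1.37 respectively, leaving 72%, 76% and 79%.

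The bias is toward zero in every scenario. Without the covariate the full effect is recovered.

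**The case against.** The strongest reply is that the adjustment is permitted rather than planned. The Co-variates sentence also mentions interpretation of the data, and the Statistical analysis section confines covariate adjustment to baseline differences, a rule that treatment given later could never satisfy. The exact covariate set may sit in an analysis plan that is not shown. This stands in part: nobody can say that the primary model will contain treatment received. But the article names the variable for adjustment in one section and leaves it unmentioned in the other, so the model remains open.

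A reader might infer that the adjustment would erase most of a true effect. The document does not support this. That result needs a count covariate and a sufficient treated share: by 25% if all children have the same treatment probability, and somewhere between 50% and 75% if propensity varies strongly. With yes/no coding most of the effect survives. Nor does an effective intervention necessarily fail the 25% rule, since the rule refers to an observed reduction and is not tied to a treatment-adjusted estimate.

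A reader might also extend the argument beyond dmfs. The ICDAS scores are described only as sound, A, B or C, with no restoration component shown. Restorations are not part of self-efficacy, brushing frequency or plaque. Varnish and sealants are outside dmfs and were not simulated. Because practices volunteer for the intervention group, and the Discussion concedes that they may be more motivated to give preventive care, preventive treatment received may partly stand in for a real practice difference. A labelled sensitivity analysis using it is defensible.

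On missed recalls, the text does not say that they enter the between-group model; a fidelity description fits it equally well.

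**Conclusion.** The concern holds for restorative treatment and dmfs. Using the adjustment that the Co-variates section provides for would condition on part of the primary outcome and bias the effect toward zero. Across the assumed scenarios the loss runs from about 3% to 98%; the treated share, its variation between children and the coding decide where it falls, and the article gives none of these. At the planning figures a loss above about 14% is enough to miss the 25% rule, provided that the rule is applied to the adjusted estimate. Even yes/no coding falls on either side of that line.

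The simulations ignore clustering and rest on assumed treated shares, so they show the direction and the possible range and do not forecast this trial. For preventive treatment the conclusion is narrower: it is a post-baseline co-intervention that should stay out of the primary effect model. For missed recalls, which can occur in one group only, the intended use needs to be stated.

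**What to change.** - **Co-variates section:** state that the primary effect analysis adjusts only for variables fixed at or before T0.0, in line with the Statistical analysis section. State that restorative treatment received is described by group and not entered as a covariate for dmfs. State that preventive treatment received is described by group and used at most in a sensitivity analysis labelled as such.
- **Contact moments section:** state that missed telephone recalls serve fidelity reporting and are not a covariate in the between-group intention-to-treat comparison.

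The cost is wording only. Extraction from the records continues as planned, and the sample size of 330 does not change. The change should be made before the T2 data are analysed, so that the choice of model cannot depend on the results.

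### The Co-variates section allows adjustment for treatment received during the study, although in-study fillings are part of the 24-month dmfs outcome

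*Protocol article*

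**What the plan says.** All places are in the protocol article.

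- **Co-variates:** after the questionnaire variables, records are to supply "restorative and preventive treatments children received during the study, to allow to adjust for this in the analysis and interpretation of data". No coding (count, yes/no, type) is given.
- **The intervention:** children in both groups may receive, "if indicated, preventive treatment (fluoride varnish and/or fissure sealants) and/or caries treatment (fillings, non-restorative caries treatment or extractions").
- **Abbreviations:** the outcome index is defined as "dmfs: Decayed, missing and filled surfaces". Under Clinical outcome, "the dmfs-index will be scored according to WHO Basic Methods for Oral Health Surveys" at T2.
- **Statistical analysis:** the primary comparison is described as "Differences in the primary outcome (dmfs and the combined ICDAS scores ‘B and C’ and ‘A, B and C"), by zero-inflated Poisson or negative binomial regression. On adjustment it says "Baseline differences in children’s dmft scores (obtained from dental records) will be taken into account", and "In case of significant differences in co-variates (moderators) between the intervention and control group at baseline (T0), the analysis will be adjusted accordingly". Treatment received during the study is neither named nor ruled out.
- **Outcome measures:** success means a 25% reduction in caries experience, equated with 1.5 to 2.0 dmfs. Better brushing outcomes cannot compensate for missing it.

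**The concern.** A covariate in an analysis of an intervention effect should be fixed before the intervention can influence it. In-study treatment is not: it is given when caries or caries risk is found, which is what the intervention is meant to reduce.

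For fillings the problem goes further. A surface that decays and is filled between T0.0 and T2 adds one to the covariate and one to dmfs. Comparing the groups at equal numbers of filled surfaces holds part of the outcome fixed, so only the untreated remainder can show a difference.

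Varnish and sealants are not counted in dmfs. For them the problem is only that they are post-baseline and may be affected by the intervention.

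At stake is the primary estimate, which decides success whatever the brushing outcomes show.

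**Working it through.** **Inputs from the document.** Power calculation: mean dmfs 6.9, SD 6.2, difference 2, 165 children per group. Outcome measures: success at a 25% reduction.

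**The plan's own figures.** A fall of 2 from 6.9 gives a ratio of 4.9/6.9 = 0.71, a 29% reduction. The success rule is a ratio of 0.75 or less: 25% of 6.9 is 1.7 dmfs, inside the stated 1.5 to 2.0. The sample size reproduces with a one-sided 5% test: 119 per group × 1.20 × 1.15 = 164.2, hence 165 and 330. A two-sided test needs 151 per group before inflation. The sample size does not affect the present point.

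**Assumptions, not in the document.** The share p of T2 dmfs surfaces that were treated during the study; whether p is the same for all children or varies between them (beta distribution, parameters summing to 2); and the coding of the covariate.

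**Model.** T2 dmfs is negative binomial with shape k = 6.9²/(6.2² − 6.9) = 47.61/31.54 = 1.51 and means 6.9 (control) and 4.9 (intervention). Treated surfaces are binomial within child. Each scenario has 60,000 children, and the group effect comes from negative binomial and linear regression. Without the treatment covariate, the ratio is 0.70 to 0.72 and the difference about −2.0.

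**With the covariate, same treatment habits in both groups** (rate ratio; linear difference in dmfs):

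| Treated share | Count, same p | Count, varying p | Yes/no, same p | Yes/no, varying p |
|---|---|---|---|---|
| 10% | 0.80; −1.23 | 0.73; −1.75 | 0.78; −1.49 | 0.73; −1.84 |
| 30% | 0.88; −0.65 | 0.77; −1.34 | 0.78; −1.54 | 0.73; −1.80 |
| 50% | 0.94; −0.34 | 0.82; −0.93 | 0.76; −1.65 | 0.75; −1.69 |
| 70% | 0.97; −0.16 | 0.88; −0.56 | 0.76; −1.69 | 0.75; −1.70 |

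At a 20% share with yes/no coding and the same p, the ratio is 0.79. Repeat runs differ by about 0.01, so the yes/no range is best read as 0.72 to 0.79.

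The log rate ratio loses, across 10% to 70%, 35% to 91% (count, same p) or 7% to 63% (count, varying p). With yes/no coding the loss stays below 30%.

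**Check by hand.** With a common p, the expected untreated surfaces given f treated ones are (1 − p)(k + f)/(k/m + p), where m is the group mean. At p = 0.5:
- control: 0.5/(0.219 + 0.5) = 0.696 per unit of (k + f);
- intervention: 0.5/(0.308 + 0.5) = 0.619.

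At the average f of (3.45 + 2.45)/2 = 2.95, the difference is −(0.696 − 0.619) × (1.51 + 2.95) = −0.34, as in the table.

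**Unequal treatment habits.** Take no true effect (mean 6.9 in both groups), with 40% treated in control and 60% in intervention practices. At f = 3.45 the same formula gives an expected dmfs of:
- control: 3.45 + 0.6/(0.219 + 0.4) × 4.96 = 8.26;
- intervention: 3.45 + 0.4/(0.219 + 0.6) × 4.96 = 5.87.

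The ratio is 0.71. Simulation gives about 0.70 (same p within group) or 0.80 (varying p), so a spurious benefit appears. With the shares reversed and a true fall of 2 dmfs, simulation gives 1.30 or 1.03, and the benefit disappears.

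**The case against.** The strongest reply is that the plan does not commit to this adjustment. The Co-variates wording is permissive and also mentions interpretation, whereas it says that the questionnaire variables need adjusting for. The Statistical analysis section limits covariate adjustment to differences at T0, which in-study treatment cannot meet, and an analysis plan not shown here may settle the matter. This stands as far as it goes: no one can say that the primary estimate will be biased. It does not remove the point, because adjustment is a stated purpose of collecting the variable and nothing excludes it from the primary model.

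A reader might infer that adjustment would remove most of a real effect. The document does not support that. It gives neither the treated share nor the coding. The loss exceeds half only with a count covariate and a share of at least about 20% (same for all children) or about 60% (varying between children).

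A reader might also infer that an effective intervention would usually be declared unsuccessful. No probability of meeting the 25% rule was calculated, and Outcome measures does not tie the rule to a treatment-adjusted estimate.

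Three limits of scope also stand:
- The Clinical outcome section describes no filled or missing category for the ICDAS scores, so the component argument covers dmfs and does not carry over directly to them.
- Extractions are listed under The intervention but not named under Co-variates.
- Recording in-study preventive care is sensible, because the Discussion accepts that intervention practices may be more motivated towards prevention. That supports reporting it, not placing it in the primary model.

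**Conclusion.** The point holds as a badly fixed rule: the article permits an adjustment that its own analysis rule would not select and that conditions on part of dmfs.

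With the same treatment habits in both groups, the bias is towards no effect. The true ratio of 0.71 moves to about 0.73 to 0.97 with a count, or about 0.72 to 0.79 with yes/no coding, for an assumed treated share of 10% to 70%. Many of these values lie above the 0.75 that the success rule requires, so an effective intervention could be judged unsuccessful. If practices in the two groups treat differently, which a non-randomised design with volunteer intervention practices makes plausible, the direction is not predictable.

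The simulation covers treated surfaces only. It gives no size for varnish or sealants, or for the ICDAS outcomes.

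**What to change.** State under Co-variates and under Statistical analysis that treatment received during the study is not a covariate in the primary analysis of the intervention effect. Adjust for baseline variables only, including baseline dmft and dmfs, which the Clinical outcome section already takes from the records. Report in-study restorative and preventive treatment by group as description. Keep any model containing in-study preventive treatment as a labelled sensitivity analysis, with a note that the variable is post-baseline.

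The cost is a change of wording before the analysis starts. It needs no extra children, visits or data.
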